## Abstract

**Background:**

Loss of teeth or occlusal imbalance is one of the proposed dental risk factors for temporomandibular disorders (TMDs). Losing some non–free-end teeth cause the original occluding tooth/teeth to supraerupt from the original upright position and causes neighboring tooth/teeth to shift in an angle, causing biomechanical imbalance on the mandible. Based on these sequelae, rehabilitation of missing teeth is the first step in managing TMD in edentulous patients. Even though the prevalence of TMD in association with edentulism and in rehabilitated patients has been increasing, proper guidelines for the management of such cases have not been established. This study describes the protocol to analyze the effect of prosthetic rehabilitation on patients with TMD.

**Objective:**

This study aims to determine the effectiveness of prosthetic rehabilitation in the reduction of pain in edentulous patients with TMD and to determine the effect of the span of edentulism, the number of quadrants involved, pathological migration, the type of Kennedy classification, and the prosthetic status on temporomandibular joint dysfunction signs and symptoms.

**Methods:**

In this randomized controlled trial, 300 patients diagnosed with TMD will be grouped into one of the three interventional groups based on the type of their edentulous state. The interventional groups are (1) partially edentulous arch: Kennedy Class I and II (prosthetic rehabilitation without splint); (2) partially edentulous arch: Kennedy Class III and IV (prosthetic rehabilitation with a splint); and (3) completely edentulous arches (prosthetic rehabilitation without splint). All three of the mentioned interventional groups have corresponding control groups that will receive symptomatic treatment and comprehensive counseling. The measured primary outcomes are pain and electromyogram, and the secondary outcomes include pain drawing, Graded Chronic Pain Scale, Jaw Functional Limitation Scale, Oral Behaviours Checklist, depression, physical symptoms, and anxiety. The outcome measurements will be recorded at baseline and at the end of 24 hours, 7 days, 28 days, and 3 months.

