#### Primary Objective

The primary objective is to determine the effectiveness of prosthetic rehabilitation in the reduction of pain in edentulous patients with TMD.

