### Outcomes

The outcome measurements will be made by an examiner calibrated according to the guidelines of DC/TMD criteria. The DC/TMD instruction video has been peer-reviewed and published [22]. Self-study guidelines and description of supervised skill development have also been described. The outcome measurements will be made at baseline and at the time points of 24 hours, 7 days, 28 days, and 3 months.

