### Sample Size

The activity of masticatory muscle (mean and SD) while chewing, estimated by EMG, reflects the TMD in a patient [35]. With a power of 80%, alpha error of .05, and effect size of 0.77, the minimum sample size estimated for each group was 22. Considering attrition and the inclusion of various variables (edentulousness location, etc), we increased the sample to 50 for each interventional group. The sample size of 50 will have a minimum of 20 patients with edentulous maxilla and 20 patients with edentulous mandible for intervention groups 1 and 2. The total sample size for the study is 300 with 150 for the interventional group and 150 for the control group. Please refer to Table 2 for the sample breakdown.

**Table 2 table2:** Sample size breakdown.

			Group 1: removable partial denture, n		Group 2: removable partial denture with stabilization splint, n		Group 3: removable complete denture, n		Total, n
**Intervention**			50		50		50		150
	Patients with edentulous maxilla	20		20		20			
	Patients with edentulous mandible	20		20		20			
	Total	40		40		40			
	Females	20		20		20			
	Males	20		20		20			
	Total	40		40		40			
**Control**			50		50		50		150
	Patients with edentulous maxilla	20		20		20			
	Patients with edentulous mandible	20		20		20			
	Total	40		40		40			
	Females	20		20		20			
	Males	20		20		20			
	Total	40		40		40			
Sample per group			100		100		100		300

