### Sequence Generation

The selected patient for trial will be randomly allocated to either the intervention arm or the control arm of their group, as per computer-generated randomization, schedule stratified, based on the type of group it belongs. The selected individuals will be allocated in equal probabilities to the intervention and control groups by stratified randomization. Stratified randomization is achieved by performing a separate randomization procedure within each of the two strata of participants. This will ensure that the numbers of participants receiving each intervention are closely balanced within each stratum. Treatment assignments are then made from separate randomization lists created in advance of the trial for each stratum.

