### Data Monitoring

An interim analysis is performed on the primary end point (reduction in pain) when 50% of patients have been randomized and have completed the 12-month follow-up. The interim analysis will be performed by an independent statistician, blinded for the treatment allocation.

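### Pain and EMG are both labelled primary, the objective rests on pain and the sample size on EMG, and no single contrast is fixed as the one that decides the trial

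*Protocol article*

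**What the plan says.** **Outcome.** The abstract states "The measured primary outcomes are pain and electromyogram", and Primary Outcome Measurements has a subsection for each. The Primary Objective section reads "The primary objective is to determine the effectiveness of prosthetic rehabilitation in the reduction of pain in edentulous patients with TMD"; the research question and hypothesis also name pain only. Data Monitoring speaks of one end point: "An interim analysis is performed on the primary end point (reduction in pain) when 50% of patients have been randomized".

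**Sample size.** The calculation is for EMG activity during chewing: "With a power of 80%, alpha error of .05, and effect size of 0.77", giving 22 per group. Then "we increased the sample to 50 for each interventional group", with a matching control of 50 each, 150 v 150 in all. No effect size is given for pain.

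**Comparison.** Under Sequence Generation a patient is "randomly allocated to either the intervention arm or the control arm of their group", from separate lists. Table 3 has a row within each arm and a row comparing groups 1, 2 and 3. It names VAS and the Graded Chronic Pain Scale as measures. It has no row for EMG and none that explicitly sets intervention against control.

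**Time.** The Outcomes section says "The outcome measurements will be made at baseline and at the time points of 24 hours, 7 days, 28 days, and 3 months". None of these visits is marked as primary. Table 3 and Data Monitoring refer to 12 months, but Participation Timeline records outcomes at five visits, the last at 3 months.

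**The concern.** A reader cannot tell from the article which result answers the trial's question. The candidates can disagree. Pain might improve in complete-denture patients at 28 days but not in group 1 at 3 months, or EMG might change while pain does not. A favourable EMG result in one group and a null pain result over all groups could each be reported as primary, with support in the text.

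This is more than the absence of a multiplicity rule, which a separate analysis plan could supply. The sections disagree on which outcome is primary, on what the trial was sized for and on when the outcome is taken. An analysis plan could choose among these, but the protocol would still contradict whichever choice it made.

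**Working it through.** **1. The plan's own figure.** Inputs from Sample Size: effect size d = 0.77, alpha .05, power 80%. Sidedness is not stated.

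- Normal approximation, n per arm = 2(z_alpha + z_beta)² / d². One-sided: 2(1.645 + 0.842)² / 0.593 = 20.9, so 21. Two-sided: 2(1.960 + 0.842)² / 0.593 = 26.5, so 27.
- With the t distribution: 21.6, so 22, one-sided; 27.5, so 28, two-sided.

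The stated 22 therefore reproduces as a one-sided two-sample test for EMG. A three-group ANOVA with f = 0.385 gives 22.7, so 23, which is close. Neither calculation concerns pain.

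**2. Which section names what.**

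| Section | Outcome | Comparison | Time |
|---|---|---|---|
| Abstract; Primary Outcome Measurements | pain and EMG | each group with its own control (abstract) | four visits (abstract) |
| Research Question, Hypothesis, Primary Objective | pain | rehabilitated v not (hypothesis) | none |
| Sample Size | EMG | per group, also 150 v 150 | none |
| Table 3, main rows | VAS and Graded Chronic Pain Scale | within arm; groups 1, 2, 3 | 12 months |
| Data Monitoring | pain | none | 12 months |

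No two of these rows agree on outcome, comparison and time together.

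**3. What the open choices could cost.** Assume that each contrast is tested at two-sided .05 and that there is no true effect. The three groups have separate patients, so they are independent. If p is the chance of at least one significant result within a group, the chance over three groups is 1 − (1 − p)³.

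- Pain, one visit: p = .05, so 1 − .95³ = 14.3%. Favourable direction only: 1 − .975³ = 7.3%.
- Pain and EMG, one visit, independent: 1 − .95⁶ = 26.5%. With correlation 0.5 between the outcomes, simulation gives p = .0911, so 1 − .9089³ = 24.9%. With correlation 0.8 it is 21.5%.
- Four visits: 200,000 simulated draws of multivariate normal test statistics, equal correlation between visits of 0.5 to 0.9, and between outcomes of 0 to 0.8. The document gives no correlations, so these are assumptions.

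| Contrasts left open | Tests | Either direction | Favouring intervention only |
|---|---|---|---|
| Pain, pooled, one visit | 1 | 5% | 2.5% |
| Pain and EMG, pooled, one visit | 2 | 8-10% | 4-5% |
| Pain, three groups, one visit | 3 | 14% | 7% |
| Pain and EMG, three groups, one visit | 6 | 22-27% | 11-14% |
| Pain, three groups, four visits | 12 | 25-40% | 13-22% |
| Pain and EMG, three groups, four visits | 24 | 37-63% | 20-39% |

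In the last row, 37% and 20% belong to visit correlation 0.9 with outcome correlation 0.8. The 63% is at 0.5 and 0.3 (64% if the outcomes are uncorrelated), and the 39% is at 0.5 and 0 (37% at 0.5 and 0.3). Full independence would give 71% and 46%.

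Under one-sided .05, which fits the stated 22, every error favours the intervention: 21-27% for 6 tests and about 34-61% for 24.

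**4. What pooling buys.** The detectable difference at 80% power, two-sided .05, is 2.802 × √(2/n). For 50 v 50 it is 2.802 × 0.200 = 0.56 SD (0.57 with the t distribution). For 150 v 150 it is 2.802 × 0.115 = 0.32 SD.

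**The case against.** The tempting stronger reading is that the protocol plans two outcomes in three groups at four visits, each at .05, and so carries up to a 60% chance of falsely claiming effectiveness. The document does not support that.

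- The four visits are a measurement schedule, not a list of tests. Table 3 names one interval. EMG has no planned test there. Alpha .05 appears once, as a sample size input.
- Pain is in effect ranked first by the research question, hypothesis, objective, interim end point and Table 3. It would be wrong to call the two outcomes wholly unranked.
- Separate randomisation lists per stratum are normal within one trial. The objective concerns edentulous patients as a whole, a 150 v 150 total is given, and the subgroup part of Table 3 lists the three groups with an interaction term. A reader may fairly infer one pooled pain contrast, and then these sources add no error.
- Under two-sided tests, only favourable errors are false claims of effectiveness, which roughly halves the figures.
- A multiplicity rule may stand in an analysis plan that is not shown.

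All of this stands, and it is why the percentages are conditional. It does not remove the contradictions. EMG is labelled primary and is the sole basis of the sample size. The pooled reading competes with sizing per group and with a main row of Table 3 that compares the groups with each other. The one interval in Table 3 ends when no outcome visit is scheduled.

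**Conclusion.** The point holds as an inconsistency in what decides the trial. The outcome, the comparison and the time point are each stated in conflicting or incomplete ways, and no section brings the three together.

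The possible error depends on how the gaps are filled. It is nominal if one pooled pain contrast at one visit is meant. It is about 14% for pain in three groups at one visit, 22-27% if EMG is added, and roughly 37-63% if all four visits are open too, for two-sided .05 tests counting either direction. For favourable results only, 6 tests give about 11-14% and 24 tests 20-39%. The first of these needs only independent groups; the ranges rest on assumed correlations. None includes the interim look. They show what the wording leaves possible, not the error rate of a stated test plan.

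**What to change.** Name one deciding contrast: intervention v control on change in pain VAS at one scheduled visit (3 months is the last), pooled over the three randomisation groups and stratified by them, at a stated alpha and sidedness. Then:

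- Make EMG a key secondary outcome, tested only if pain is positive.
- Report group-specific effects as supportive estimates with 95% intervals and one treatment-by-group interaction. Group 2 also receives a splint, so the pooled effect averages over different packages and the report should say so. If a claim per group is wanted, use Holm over the three groups.
- Label the other visits supportive.
- Add the intervention v control row to Table 3.
- Reconcile the abstract, Primary Outcome Measurements, Sample Size, Table 3 and Data Monitoring, including 12 months v 3 months. Sample Size should say what 150 v 150 can detect for pain, or that it was set on EMG.

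This is wording only and needs no new patients or data, but it should be settled and dated before anyone sees results by arm. The price is that EMG and single-group results lose stand-alone confirmatory status. With Holm, the strictest step (.0167) at 50 v 50 detects (2.394 + 0.842) × 0.200 = 0.65 SD, against 0.32 SD for the pooled test. Whether either is adequate for pain cannot be judged, because no pain effect size is given.

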**Results:**

Ethical approval was obtained from the Institutional Review Board of Amrita Institute of Medical Sciences, Kochi, India. Study participants’ recruitment began in May 2021 and is expected to conclude in March 2023. This clinical trial protocol was developed based on the SPIRIT (Standard Protocol Items: Recommendations for Interventional Trials) 2013 Statement.

**Conclusions:**

The purpose of this study is to gather data on prosthetic rehabilitation as a treatment for TMD. Obtaining this goal will aid in the development of evidence-based therapy protocols for prosthetic rehabilitation in TMD management.

**Trial Registration:**

Clinical Trials Registry - India CTRI/2020/06/026169; http://ctri.nic.in/Clinicaltrials/pdf_generate.php?trialid=42381

**International Registered Report Identifier (IRRID):**

DERR1-10.2196/33104

## Introduction

### Background

Temporomandibular disorders (TMDs) are defined by the American Academy of Orofacial Pain as “a collective term that embraces a number of clinical problems that involve the masticatory muscles, the temporomandibular joint, and the associated structures” [1]. TMDs are characterized by clinical signs such as muscle and/or temporomandibular joint tenderness; temporomandibular joint sounds (clicking, popping, or grating) while opening or closing the mouth or while chewing; and restriction, deviation, or deflection of the mouth while opening or closing [1].

The sum or exacerbation of these signs and symptoms eventually limits or even disables individuals in their physiological activities [2]. Between 40% to 75% of the population has at least one TMD sign such as noise in the temporomandibular joint, and 33% have at least one symptom, facial pain, or temporomandibular joint pain [3]. Between 65% to 85% of humans experience some symptoms of temporomandibular joint dysfunction at some time during their life, and 5% to 7% of the whole population requires treatment to decrease the symptoms of TMD [4]. Due to the high variability in the presentation of this disorder, TMD is diagnosed by its associating signs and symptoms [5,6].

TMD have been identified as a major cause of orofacial pain of nondental origin [7]. The World Health Organization has emphasized the importance of being free of chronic orofacial pain as a clear prerequisite for oral health as well as the negative effect of functional problems, such as chewing and eating, on the individual’s well-being and daily living, making them determinants of oral and general health [8]. Individuals with TMD symptoms have been found to seek different care providers and use the health care system to a greater degree as well as being more frequently on sick leave than people without these conditions [9]. Patients with TMD consequently experience a considerable negative effect on their quality of life [10].

TMDs have a complex and multifactorial etiology. One contributing factor that has been debated for years is the “occlusal condition” of the patient [10]. Loss of teeth or occlusal imbalance is one of the proposed dental risk factors for TMD. These dental factors include posterior crossbite, overjet/overbite greater than 5 mm, centric relation/maximum intercuspal sliding greater than 2 mm, edge-to-edge bite, sagittal relation class III, anterior open bite, and missing teeth [11,12]. Teeth are the most important components of the masticatory system with a close relationship with the temporomandibular joint and masticatory muscles. Any change to their normal functioning can induce pathological changes in the temporomandibular joint. *Missing posterior teeth* has been shown to have varied effect on the incidence of TMD [13-15].

Loss of teeth without replacement, especially at an early age, often causes the original occluding tooth/teeth to supraerupt from the original upright position and causes the neighboring tooth/teeth to shift in angle. Once the tooth/teeth begin to shift in angle, the vector of force tends to increase tooth-/teeth-tilting, thus imposing a different biomechanical effect on the mandible [16]. There is gender predilection, wherein the female mastication system may have less ability to withstand harmful stimulation from abnormal occlusion compared to counterparts, and thus, females may be more susceptible to TMD than men [17].

Little has changed in terms of study designs for temporomandibular joint research in the last decade, and treatment for patients with severe TMD remains controversial [18]. Following loss of occlusion due to tooth loss, there are secondary changes in the temporomandibular joint, which may accentuate further signs and symptoms [19]. The scientific community is uncertain about occlusion as the dominant cause of TMD nor do they justify prosthetic rehabilitation as the primary treatment modality for the management of TMD. The irony is that even though there is lack of evidence for loss of occlusion as a cause of TMD, the standard protocol in the management of TMD with edentulism is prosthetic rehabilitation.

There are still disagreements over the most effective and cost-effective treatment approach that can be widely distributed and used [20]. It is based on the clinical experience that, as the teeth are the most important components of the masticatory system and as they have a close relationship with the temporomandibular joint and masticatory muscles, any change to their normal functioning can induce pathological changes in the temporomandibular joint. Although prosthetic rehabilitation is the primary step in managing TMD, it is hardly justified with the evidence in the literature. With these gaps in knowledge regarding occlusion as a causative factor for TMD in the literature, we designed this trial to generate evidence regarding prosthetic rehabilitation for the management of TMD. Achieving this objective will help to develop the evidence for a treatment protocol for prosthetic rehabilitation in the management of TMD.

There are 3 intervention groups and their corresponding 3 control groups. The study has prosthetic rehabilitation with or without a splint (intraoral appliance) as the intervention. The comparator agent is symptomatic treatment and comprehensive counselling. If the patient is diagnosed with jaw joint disorder and has missing teeth, and if they are willing to take part in the study, they will be grouped into one of the three interventions or one of the three control groups based on the type of the toothless condition.

### Objectives

#### Research Question

Can prosthetic rehabilitation of edentulous patients with TMD decrease the pain symptoms of TMD?

#### Hypothesis

Prosthetic rehabilitation of edentulous patients will reduce pain symptoms of TMD as compared to patients without rehabilitation.

#### Primary Objective

The primary objective is to determine the effectiveness of prosthetic rehabilitation in the reduction of pain in edentulous patients with TMD.

#### Secondary Objective

The secondary objective is to determine the effect of the span of edentulism, the number of quadrants involved, pathological migration, the type of Kennedy classification, and the prosthetic status on temporomandibular joint dysfunction signs and symptoms.

### Trial Design

This trial is designed as randomized, as controlled, with a parallel arm, as blinded for outcome measurement, and with adaptive trial design.

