#### Primary Outcome Measurements

##### Pain

Pain will be measured using the visual analog scale (VAS) for pain. The pain VAS is a unidimensional single item measure of pain intensity [23], which has been widely used in diverse adult populations. Using a ruler, the score is determined by measuring the distance (mm) on the 10-cm line between the “no pain” anchor and the patient’s mark, providing a range of scores from 0 to 100 [24].

For pain intensity, the scale is most anchored by “no pain” (score of 0) and “pain as bad as it could be” or “worst imaginable pain” (score of 100 on a 100-mm scale). The following cut points on the pain VAS will be used: no pain (0-4 mm), mild pain (5-44 mm), moderate pain (45-74 mm), and severe pain (75-100 mm) [25].

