### Allocation Concealment Mechanism

Allocation concealment will be ensured, the randomization code will not be released until the patient has been recruited into the trial, which takes place after all baseline measurements have been completed. The randomized codes, kept in a sealed cover at each clinic, will assign the patient to the intervention at baseline visit. The statistician will design the randomization schedule.

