### Implementation

The randomization will be conducted by a statistician to manage the data, and the statistician will be blind against the study condition. The randomization list will remain with the doctoral committee for the whole duration of the study. Thus, randomization will be conducted without any influence of the dentist and hygienist.

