### Blinding

Due to the obvious nature of the treatment, neither the treating dentist or patients are blinded; patients are only randomly allocated to the intervention. However, the data analyst or statistician will be blinded during the statistical process.

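### The trial is described as blinded for outcome measurement, which cannot be true of patient-reported pain and has no stated support for the EMG and DC/TMD assessments

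*Protocol article*

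**What the plan says.** The Trial Design section lists the design features in one sentence, and one of them is that the trial is described "as blinded for outcome measurement".

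The Blinding section states that "neither the treating dentist or patients are blinded; patients are only randomly allocated to the intervention". The protection it then offers is that "the data analyst or statistician will be blinded during the statistical process". It does not mention the person who measures the outcomes.

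There are two primary outcomes. For pain, the VAS score is the distance between "the “no pain” anchor and the patient’s mark". For EMG, the protocol specifies posture and electrode placement but nothing about masking whoever records or reads the signal. On the assessor, the Outcomes section says: "The outcome measurements will be made by an examiner calibrated according to the guidelines of DC/TMD criteria".

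The other mentions of blinding also concern statisticians. Under Implementation, "the statistician will be blind against the study condition"; under Data Monitoring, an independent statistician does the interim analysis without knowledge of the allocation.

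**The concern.** Blinding the analyst protects the analysis. It does not protect the measurement, which is what the Trial Design sentence claims. A reader who takes that sentence at face value will credit the pain result with a safeguard it does not have.

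This matters because the comparison is a denture, with or without a splint, against symptomatic treatment and counseling. Patients know which they received. Those who were given a prosthesis may report less pain for that reason alone, and an examiner who sees the prosthesis may measure differently. Both would tend to favour the intervention. Pain is the subject of the research question, the hypothesis, the primary objective and the interim analysis, so the misdescription touches the main result.

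**Working it through.** The check is mainly a comparison of sections; the protocol states no figure to reproduce.

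**Pain VAS.**
1. The patient makes the mark that is the measurement (Pain section).
2. The patient knows the allocation (Blinding section).
3. The assessor of this outcome is therefore unblinded. A masked person reading the ruler would not change that, because the mark is already made. The Trial Design claim is false for pain.

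**EMG and DC/TMD examination.**
1. The Trial Design section asserts blinding. No other section says who is masked for these measurements or how.
2. The Outcomes section requires calibration, which gives consistency between examinations, not ignorance of the arm.
3. The Blinding section names the analyst or statistician as blinded and leaves out the examiner.
4. Table 1 has a single row for DC/TMD assessment, EMG and review of the prosthesis, marked for all six visits. The Interventions section gives controls no prosthesis, so a new denture or splint would usually reveal the arm to anyone examining the mouth.
5. No section says that the examiner is unblinded or is the treating dentist. The claim is thus unsupported, and implausible as scheduled, but not contradicted outright.

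**Illustration of what reporting bias could do to the VAS.** The documents give neither a bias nor an SD for the VAS, so both are assumed. With no true effect, bias b and n per arm:

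z = b / (SD × √(2/n)); chance of a significant result = P(Z > 1.96 − z) + P(Z < −1.96 − z), two-sided .05.

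| Assumed bias and SD | b/SD | n per arm | z | Chance of significance |
|---|---|---|---|---|
| 5 mm, 25 mm | 0.20 | 50 | 0.20/0.200 = 1.00 | 17% |
| 5 mm, 25 mm | 0.20 | 150 | 0.20/0.115 = 1.73 | 41% |
| 3 mm, 25 mm | 0.12 | 50 | 0.12/0.200 = 0.60 | 9% |
| 8 mm, 20 mm | 0.40 | 50 | 0.40/0.200 = 2.00 | 52% |

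The arm sizes of 50 and 150 are those in the Sample Size section. A larger sample does not protect against such a bias; it makes a biased difference more likely to reach significance.

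**The case against.** The best reply is that the article is a condensed protocol. The Outcomes section speaks of an examiner, a different term from treating dentist, and the Blinding section does not say that only the statistician is blinded. Read with the Trial Design sentence, this could mean a masked examiner whose procedure is described in the full protocol. For EMG and DC/TMD that reply has force, and it is why the point there is lack of support and not contradiction. A reader might infer that both primary outcomes are shown to be assessed unblinded, or that the treating dentist does the measuring; the documents establish neither. For pain the reply fails, because no examiner procedure can mask a mark made by an unblinded patient.

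A reader might also infer that the analyst's blinding is compromised, since "The statistician will design the randomization schedule". The documents do not support that either. The list stays with the doctoral committee, the text does not say that the person who designs the schedule also analyses the data, and a separate blinded statistician does the interim analysis. In any case that question concerns the analysis, not outcome measurement.

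Finally, the Blinding section openly admits that patients are unblinded, and open-label self-report is often unavoidable with a visible prosthesis. That stands. The fault is the claim in the Trial Design section, not the choice of a self-reported outcome.

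**Conclusion.** The concern holds in two parts of different strength. For the pain VAS, the description of blinded outcome measurement is wrong as written; this follows from the Pain and Blinding sections and needs no assumption. For EMG and the DC/TMD examination, the description has no stated support and is implausible for anyone who examines the mouth; this rests on what the article does not say and on the layout of Table 1.

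The size of any bias cannot be obtained from the documents. The range of 9% to 52% with 50 v 50 rests on an assumed bias of 3 to 8 mm and an assumed SD of 20 to 25 mm. It shows why an open-label pain result needs cautious reading. It does not measure what the correction would gain, because rewording leaves the patients' reporting as it is.

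**What to change.** - Restate the Trial Design sentence: open label for patients and treating dentists; pain VAS self-reported and unblinded; blinding limited to EMG quantification and the statistical analysis. Bring the Blinding section into line.
- Store EMG recordings under the participant code and have them quantified by someone without access to the arm.
- Have someone other than the treating dentist do the EMG and DC/TMD assessments, apart from the prosthesis review where feasible. If the prosthesis is visible at the DC/TMD examination, describe that examination as unblinded.
- Add self-report bias in the VAS to the Strengths and Limitations section.

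The cost is coding of EMG files, some separation of tasks at visits, and a less favourable design description. Coded reading protects the quantification of EMG but not its recording, and nothing here removes self-report bias in pain.
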